### Recruitment

We aim to recruit approximately 50 families over a period of 24 months (2015–2017) at the two participating centres. Potentially eligible families will be identified using existing waitlists within each site, as well as through liaison with a range of other statutory and community-based services in the area, who may also refer potential participants to the participating sites. Voluntary self-referrals will be accepted if the participating site deems that the family meets the inclusion criteria for the study. Many of the families involved in the study will most likely have an allocated social worker. Each site will meet with eligible families to discuss the intervention and the research evaluation. Families will be given a brief information sheet inviting them to receive further information about the study, and requesting that they provide their consent to forward their contact details to the research team. Participants will then be contacted by telephone to arrange for the research interviewer to visit them at home and to inform them about the study and obtain their written informed consent. Written informed consent will be obtained before any study-specific procedures, including collection of baseline data. Families will be thanked for their time and given a shopping voucher worth €20 at each data-collection visit. Collectively, the research team have considerable experience of working with vulnerable and difficult-to-engage populations and their expertise, in conjunction with the advice and support of the collaborators, will be important in managing the recruitment process.

### Procedure

***Study design.*** The ChARM study is a randomised controlled, parallel group, investigator-blinded, superiority trial (n = 50) comparing the ChARM intervention with usual services (1:1 allocation ratio), and a primary endpoint of incidences of child maltreatment and child wellbeing at six-month follow up. Data will be collected at three time points: T1 (pre-intervention), at six-month follow up (T2; one-month post intervention), and at 12-month follow up (T3). Assessment of the control group will continue to T2, after which they will receive the ChARM programme. Assessment of the intervention group alone will continue to T3. We will follow CONSORT guidelines for reporting parallel group randomised trials (
Moher *et al.*, 2010).
Figure 1 shows the study flow diagram.

**Figure 1. f1:**
[figure not shown]
Study Flow Diagram.

The embedded process evaluation - in line with the guidelines of the Medical Research Council (MRC) - aims to develop a logic model of the ChARM programme, elucidating key processes in programme development and implementation, impacts and outcomes (
Moore *et al.*, 2014; see
Supplementary Figure 2). Specifically, it will aim to:

•  Identify key programme content and perceived mechanisms of change;

•  Assess enablers and barriers to programme development and implementation within the trial;

•  Evaluate fidelity of delivery and participant engagement; and

•  Investigate the feasibility of implementing the programme among services not involved in the trial

The embedded costs analyses will include a cost effectiveness analysis (CEA) and a cost-benefit analysis (CBA). The CEA will be based on a societal perspective (involving public sector costs, and costs incurred by participants in attending the programme) and will assess the costs of delivering the ChARM programme compared to usual services. If the intervention demonstrates effectiveness, the CBA will investigate the down-stream impact of the intervention on later costs, such as generating savings in relation to reduction in child welfare services, foster and residential placements, health and mental health service utilization, crime, education and unemployment.

### Randomisation and blinding

Participants will be randomly assigned by an independent statistician (in the Northern Ireland Clinical Trials Unit [NICTU]) to either the ChARM programme or to standard services with a 1:1 allocation using a computer-generated randomisation schedule stratified by site using permuted blocks of random sizes. The NICTU will use sequentially numbered, opaque, sealed envelopes to conceal the randomisation code until the participant has been recruited into the trial, which will take place following completion of baseline assessments. Block sizes will be concealed throughout the duration of the study. Throughout the study, randomisation will be conducted by the NICTU in order to keep the data management and the statistician blind against the study condition as long as the data bank is open. The randomisation list remains with the NICTU for the duration of the study. Thus, randomisation will be conducted without any influence of the principal investigator, data collectors or practitioners delivering the intervention.

Follow-up assessments at T1 and T2 will be performed by research staff blinded to study arm. At T3, we will only collect data from intervention families so blinding will not be relevant. At T2, participants will be requested not to disclose their group allocation to the researcher. If unblinding occurs, another assessor will be brought in to re-establish blindness. Any evidence of unmasking of blinding will be taken into account at the analysis stage. Due to the nature of the intervention, neither participants nor practitioners can be blinded to allocation.

### Contamination

To reduce the risk of contamination between the intervention and control participants within sites, staff who deliver the ChARM intervention will not be involved in delivering usual services to families in the control group. In addition, practitioners in both the intervention and control groups will be asked about the extent to which they shared with each other/learned of content from the ChARM programme and passed this information to families in the control group. If levels of contamination are found to be high in the control group, an extra confounder variable denoting contaminated controls will be added to the analysis and the effects of this contamination investigated.

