## Abstract

The prevention of child abuse and neglect is a global public health priority due to its serious, long-lasting effects on personal, social, and economic outcomes. The Children At Risk Model (ChARM) is a wraparound-inspired intervention that coordinates evidence-based parenting- and home-visiting programmes, along with community-based supports, in order to address the multiple and complex needs of families at risk of child abuse or neglect. This paper presents the protocol for a study that will be carried out to evaluate this new service model (i.e. no results available as yet). The study comprises a multi-centre, randomised controlled trial, with embedded economic and process evaluations. The study will be conducted in two child-welfare agencies within socially disadvantaged settings in Ireland. Families with children aged 3-11 years who are at risk of maltreatment (n = 50) will be randomised to either the 20-week ChARM programme (n = 25) or to standard care (n = 25) using a 1:1 allocation ratio. The primary outcomes are incidences of child maltreatment and child behaviour and wellbeing. Secondary outcomes include quality of parent-child relationships, parental stress, mental health, substance use, recorded incidences of substantiated abuse, and out-of-home placements. Assessments will take place at pre-intervention, and at 6- and 12-month follow-up periods. The study is the first evaluation of a wraparound-inspired intervention, incorporating evidence-based programmes, designed to prevent child abuse and neglect within high risk families where children are still living in the home. The findings will offer a unique contribution to the development, implementation and evaluation of effective interventions in the prevention of child abuse and neglect.

The trial is registered with the International Standard Randomised Controlled Trial Number Register (DOI 10.1186/ISRCTN13644600, Date of registration: 3
^rd^ June 2015).

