### Data analysis

***RCT.*** Changes in continuous primary and secondary outcomes at baseline and at six-month follow-up will be compared for the intervention and control groups using ANCOVA, controlling for intervention status, site, baseline score and any other baseline differences identified. Mean difference effect sizes, 95% confidence intervals (CIs), and p values will be reported for continuous outcomes. Changes at 12-month follow up will be conducted using ANOVA. Changes between study arms in categorical variables (i.e. data records of incidences of CM and out-of-home placements) at baseline and six-month follow up will be analysed using the Chi Square test of independence, reporting relative risk, 95% CIs and p values. Descriptive statistical summaries (e.g. means, standard deviations, frequencies) will be presented for primary and secondary outcome measures at each time point. All data for primary and secondary outcomes will be analysed using an intention-to-treat analysis, using multiple imputation (MI) to compensate for missing data at different assessment points. Imputation assumptions for MI will be reported and justified, and imputed data analysed as part of a sensitivity analysis. Parallel per protocol analyses will also be conducted for outcomes. Attrition analyses will be conducted at each time point to assess for differences between those who dropped out from the programme me and those who stayed. This will be based on an examination of key baseline variables (e.g. intervention arm, participant SES and wellbeing, child gender) and qualitative data outlining reasons for attrition.

Multiple regression techniques will be used to explore moderators of intervention effects (if present). Moderators will include: severity of risk and CM at baseline (measured using below and above clinical cut-off scores on the BCAPI, CTSPC, as well as frequency of CM incidences within substantiated reports); age and SES of parents and children (measured using a composite risk factor score derived from demographic data on the Profile Questionnaire); gender of child; parental mental health and problem substance use (using above or below clinical scores on the DASS, CAGE and DAST). Statistical analyses will be conducted using SPSS and Stata. We are aware of the possibility of low statistical power given that our numbers are lower than desired. Hence these analyses will be more exploratory in nature.

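### A post-randomisation 'contaminated controls' indicator in the ANCOVA makes the treatment coefficient ChARM versus unflagged controls only, against the stated intention-to-treat principle and open to bias in either direction

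*Protocol article*

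**What the plan says.** The Contamination section of the protocol article begins with prevention: staff who deliver ChARM will not serve control families. It then says how contamination will be learned: "practitioners in both the intervention and control groups will be asked about the extent to which they shared with each other/learned of content", and whether that content was passed on to control families. The contingency follows. "If levels of contamination are found to be high in the control group", then "an extra confounder variable denoting contaminated controls will be added to the analysis and the effects of this contamination investigated". The section gives no level that counts as high. It does not say whether the model with the extra variable is the main analysis or a supplementary one.

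The Data analysis section sets an ANCOVA for continuous outcomes at six months, "controlling for intervention status, site, baseline score and any other baseline differences identified". It adds: "All data for primary and secondary outcomes will be analysed using an intention-to-treat analysis". The contamination variable is not mentioned there. Randomisation and blinding states that "neither participants nor practitioners can be blinded to allocation". The Abstract gives the arm sizes: families "will be randomised to either the 20-week ChARM programme (n = 25) or to standard care (n = 25) using a 1:1 allocation ratio".

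**The concern.** A confounder of a treatment comparison has to be related to how treatment was assigned. Here assignment is random, and contamination happens afterwards. It is also structurally tied to one arm, because no ChARM family can be a contaminated control. Putting such a variable in the model does not remove a baseline imbalance. It gives the flagged controls their own intercept and so takes them out of the treatment contrast. What remains is the whole ChARM arm against a subset of controls chosen by something that happened during follow-up.

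Two features add to the problem. Practitioners who know the allocation supply the flag, and whether the model changes at all depends on a judgement, made without a threshold, that contamination was high. At stake is the treatment estimate for both primary outcomes: it would no longer be the effect in all families as randomised, and its error rate would no longer be controlled.

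**Working it through.** **Inputs from the protocol article.** 25 families per arm (Abstract); ANCOVA with treatment and baseline score (Data analysis); a control-only flag (Contamination). The article gives no contamination rate or effect, so there is no figure of its own to reproduce.

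**Assumed inputs, shown as ranges.** The outcome is oriented so that a positive difference favours ChARM.
- f, share of controls flagged: 0.2 to 0.4
- g, benefit that contamination passes to flagged controls: 0 to 0.3 SD
- s, prognosis of flagged minus unflagged families, left after baseline adjustment: -0.5 to +0.8 SD
- d, true effect: 0 or 0.4 SD
- baseline-outcome correlation: 0.5, so residual variance 0.75

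**Step 1: what the coefficient estimates.** With treatment T and flag C in the regression, and C = 1 only in controls, the coefficient of T is the ChARM mean minus the unflagged-control mean. In an example with 25 ChARM families and 25 controls, 10 of them flagged, the coefficient was 0.2121. The ChARM mean minus the mean of the 15 unflagged controls was also 0.2121. The difference between the arms as randomised was 0.0779. When baseline score or site is added, flagged controls contribute only to those terms.

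**Step 2: expected values.**
- All randomised families: d - f × g
- With the flag: d + f × s
- Shift caused by the flag: f × (g + s)

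The shift favours ChARM only when g + s is positive. With no true effect, the bias is f × s, and its sign is the sign of s.

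**Step 3: no true effect, g = 0, f = 0.4, 4,000 simulated trials per row, two-sided 5% test.**

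| s (SD) | f × s | Simulated estimate with flag | Rejection with flag | Rejection without flag |
|---|---|---|---|---|
| -0.5 | -0.20 | -0.21 | 10.5% (mostly against ChARM) | 5.7% |
| 0 | 0 | -0.01 | 5.6% | 5.8% |
| +0.5 | +0.20 | +0.19 | 9.9% | 5.1% |
| +0.8 | +0.32 | +0.31 | 17.0% | 5.1% |

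At f = 0.2 the estimates with the flag run from -0.10 to +0.15 SD and rejection from 5.2% to 8.9%. Without the flag and with g = 0, rejection was 4.8% to 6.0% at every f and s tried.

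**Step 4: precision at f = 0.4, s = 0.** All controls: √(0.75 × (1/25 + 1/25)) = 0.245. With 15 unflagged controls: √(0.75 × (1/25 + 1/15)) = 0.283. The simulated values were 0.246 and 0.287.

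**Step 5: a true effect with real contamination, d = 0.4, f = 0.4, g = 0.3.** All randomised families: 0.4 - 0.4 × 0.3 = 0.28. With the flag: 0.40 at s = 0, 0.4 + 0.4 × 0.5 = 0.60 at s = +0.5, and 0.4 - 0.4 × 0.5 = 0.20 at s = -0.5. The simulated values were 0.39, 0.59 and 0.20.

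**The case against.** A reader might infer that the rule must favour ChARM, on the view that the controls who pick up programme content are the more engaged families. The article does not support that. The route it describes runs through practitioners who share or learn content and pass it on, and it says nothing about the prognosis of the families reached. Closer practitioner contact could equally mark harder cases, and then the bias runs against ChARM. If flagging is unrelated to prognosis (s = 0), the flagged model has the correct type I error and recovers the undiluted effect, 0.40 against 0.28 in Step 5. Adjustment for baseline score also absorbs part of any prognostic gap, so the larger values of s are demanding.

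A reader might also infer that the flagged model replaces the intention-to-treat analysis. The article does not say so. The covariate list under Data analysis omits the flag, and the closing words about investigating the effects of contamination could describe a supplementary look. The rule is conditional, staff are separated to make contamination less likely, and the Discussion calls the trial exploratory.

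All of this stands, but it does not remove the defect. The article says the variable will be added to the analysis, calls it a confounder, and nowhere labels the result a sensitivity analysis or says that the all-randomised result remains primary. The favourable case s = 0 cannot be verified from trial data. If flags follow caseworkers rather than families, a different cost can appear: with site in the model, flagging every control at one site reduces the treatment coefficient to the other site's difference alone.

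**Conclusion.** The point holds. A stated rule, if followed, makes the treatment coefficient a comparison of all ChARM families with a post-randomisation selection of controls, and this contradicts the intention-to-treat statement. Under the assumptions in Step 3, the bias is about -0.2 to +0.3 SD and two-sided type I error about 6-17%, against about 5-6% without the flag. The standard error also rises by roughly a sixth (0.287/0.246 = 1.17), in a trial that its Sample size section already describes as smaller than advised. These sizes depend on the assumed flagged share and prognostic gap. The change in what is estimated does not depend on them.

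The conclusion does not extend to unmasking. The Randomisation and blinding section says "Any evidence of unmasking of blinding will be taken into account at the analysis stage", and a reader might infer the same kind of covariate adjustment. That sentence names no variable, model or exclusion. Descriptive reporting or a sensitivity analysis would satisfy it, so no error can be attributed to it.

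**What to change.** In the Contamination section, remove the word confounder and state that the ANCOVA of all randomised ChARM families against all randomised control families stays primary whatever the level of contamination. Report contamination descriptively by site. If a contamination-adjusted estimate is wanted, define contamination and the level that triggers the analysis in advance, and label the result a sensitivity analysis. Preferably use a method with randomisation as the instrument, such as a complier-average effect. State its assumption openly: a control family that received second-hand content is counted as treated, although that is far from the full 20-week programme. The estimate would also be imprecise at 25 per arm.

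The cost is a few sentences and no new data. The downside is that the primary estimate stays diluted if contamination is real (0.28 rather than 0.40 SD in Step 5). That dilution belongs to the intention-to-treat answer, and the descriptive report lets readers judge it.

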### Intervention

The ChARM programme involves the coordination of three ‘core’ components, as well as additional services and supports (formal and informal) that will be provided to families, as necessary (See
Figure 2). The core components include: (1) the Positive Life Skills Programme (PLSP); (2) the Incredible Years Parenting Programme (IYPP); and (3) home visits. Both the PLSP and home visits may be used to initially engage families, although not all families will require home visiting as a means of engagement. Home visits will be conducted concurrently with the delivery of the PLSP and the IYPP. The programme will last 20 weeks. More details on the programme components are provided below.

**Figure 2. f2:**
[figure not shown]
Core Components of ChARM Programme. ChARM involves an intensive package of supports for families inspired by a wraparound philosophy of care. It comprises core components of parent training, home visits, a positive life skills programme and additional supports as desired by families.

***Coordination of supports.*** Each family will be already linked to a caseworker (social worker, family support worker) informed of the wraparound approach. The caseworker will discuss the suitability of the ChARM intervention with the family. Families must consent to engage with the three core components of the programme. Family strengths and needs will be examined and families will have an opportunity to identify other services and supports, besides the three core components, that may help them to achieve their goals. If any issues emerge during the family’s participation in the ChARM, additional services will be provided/recommended. The caseworker for intervention families in this study will also be a facilitator of the group programme s within the intervention.

***The Positive Life Skills Programme - PLSP.*** The PLSP is a manualised four-week, two-hour, parent-group programme, developed as a brief intervention to encourage vulnerable, hard-to-reach parents to engage with services. Many ‘at risk’ families suffer from mental health, addiction and other issues and consequently, parents may not possess the skills and self-esteem to engage constructively with needed services and supports. Sessions are delivered by two group facilitators who are trained in programme delivery. The four sessions help parents to: engage in a group setting with other parents and with service providers in a therapeutic space that allows sharing of personal issues; develop confidence, self-esteem and resilience in engaging with services; and build skills for daily living, including developing communication, stress and conflict management skills.

***The Incredible Years Parenting Programme – IYPP.*** The IYPP is a well-known evidence-based parenting programme that has demonstrated effectiveness in improving child emotional and behavioural problems, and parental mental health, within high-risk populations (
Furlong *et al.*, 2012). Recent studies of a clinically-informed adaption of the programme for families within the child welfare system have indicated preliminary evidence for improved parenting practices (
Hurlburt *et al.*, 2013;
Letarte *et al.*, 2010). The IYPP consists of 14 weekly, 2-hour, parent-group training sessions, and topics include: learning to play with the child; social and emotional coaching methods; increasing positive behaviour through praise and incentives; problem-solving; and managing non-compliance and aggression through limit setting, ignoring, and other strategies. The sequence of topics for child welfare populations is similar to standard IYPP protocols, but has a greater focus on parent-child attachment, emotional and social coaching, parental attributions and self-talk, monitoring and self-care, along with increased dosage and home visits, if necessary (
Webster-Stratton & Reid, 2010). Sessions use dvds, role-play, modelling, group discussions, homework assignments and mid-week phone-call support to help parents rehearse and adopt positive parenting strategies. The IYPP addresses access issues and advocates provision of transportation, childcare and meals to parents. The programme also encourages parents to set up peer networks outside of group sessions in order to promote connections to the community and to increase the self-sufficiency of parents (
Webster-Stratton & Hancock, 1998). Within the ChARM programme, the IYPP will be delivered following the PLSP.

***Home visits.*** Home visits will be provided in parallel to the delivery of the PLSP and the IYPP, although in some cases, families will receive home visits before the PLSP in order to engage them to the ChARM programme. Family support workers will visit family homes and coach parents in positive parenting practices. Home-visiting sessions will reinforce the positive parenting principles taught in the IYPP using similar content, role-play and vignette strategies, as outlined in the IY home-visiting coaching model (
Lees *et al.*, 2014). They may also link families into other services, teach them how to complete housework or to seek social support when necessary, such as in transporting children to activities. The number of home visits per family will vary, as some families will require significantly more assistance than others. We will document the number of home visits received by families.

***Additional supports.*** Families at risk of CM present with a number of complex needs, including: substance abuse, mental health problems, health difficulties, educational deficits, unemployment, child disabilities, and so forth. The components outlined above may not be able to deal effectively with these issues. Consequently, caseworkers will collaborate with families in order to help them engage with relevant community-based agencies to address such issues. The additional supports may include, but are not restricted to, outreach activities, resilience and social skills training, housing and financial advice, referral to a substance abuse clinic, therapeutic services for family members, and so forth. Families will also be encouraged to utilize informal supports. The type and frequency of services and supports received by families will be documented as part of the costs and process evaluations conducted within the context of this study.

***Services as usual.*** Standard services will be provided by the child welfare and protective system in Ireland and may vary by site and family need. Families in the comparison condition will be assigned a caseworker who will arrange referrals to appropriate services as required, e.g. referral to substance abuse clinic or adult mental health centre. The type and amount of services received by families in the control condition will be documented by the research team. Families in the control group will be offered the ChARM programme at T2, i.e. at six-month follow up.

